**Provider participants**		
	Inclusion	All emergency physicians, nurses, physician assistants, and nurse practitioners who work in the study emergency department will have access to the E-IPPs as routine practice and physicians are asked to complete baseline surveys at enrollment for research purposes
	Exclusion	None

^a^IPP: individualized pain plan.

^a^E-IPP: electronic health record–embedded individualized pain plan.

### Recruitment

#### Patient Recruitment and Procedures

Potential participants will be approached in person, by phone, or via electronic media about enrolling in the study. All patients enrolled in the Sickle Cell Disease Implementation Consortium registry and screened as eligible will be contacted by research staff for participation in the emergency department project. Additional participants meeting criteria at participating Sickle Cell Disease Implementation Consortium sites not previously enrolled in the registry are also eligible and may be recruited in the clinic, during hospitalizations, or at community events by research staff. Patient participants will provide informed consent before study participation.

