**Patient participants**		
	Inclusion	Confirmed sickle cell disease diagnosis, defined as supported by documentation in the medical record of a positive test for 1 of the following genotypes: Hb SS, Hb SC, Hb Sβ-thalassemia, Hb SO, Hb SD, Hb SG, Hb SE, or Hb SF. If no medical record is available, the enrolling site will conduct its own laboratory test as confirmation English speaking Age 18-45 years (National Heart, Lung, and Blood Institute grant requirement) Access to either an Android or iOS cellular or mobile smartphone, with access to text messaging and internet At least 1 vaso-occlusive episode visit to the participating site’s emergency department within the past 90 days prior to enrollment At least 1 visit at the study site sickle cell disease clinic within the past 12 months Willing and cognitively able to give informed consent
	Exclusion	Site hematologist or sickle cell disease provider states patient should not have a protocol or should not be administered opioids

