#### Provider Recruitment

All emergency department providers will be able to access the E-IPPs and will receive training on the protocol at staff meetings, resident conferences, or through emails. All emergency department providers will be invited to complete a baseline survey at enrollment with an information sheet introducing the study. If an enrolled patient participant has a qualified emergency department visit and the corresponding emergency department provider has not received training or completed the baseline survey, the study team will send a provider follow-up survey to the provider at enrollment with an information sheet introducing the study.

A qualified emergency department visit is defined as (1) a visit for an enrolled patient to a participating emergency department, the reason for the visit is a vaso-occlusive episode, and the patient has an E-IPP at the time of the emergency department visit; and (2) the patient’s first emergency department vaso-occlusive episode visit of the month, after enrollment, within the 12 month study period for that patient.

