### Patient Baseline and Follow-up Survey

Each participating site will administer a brief patient baseline survey at the time of patient enrollment that will assess patient demographic data, patient-perceived quality of emergency department pain treatment for the last emergency department visit (within 90 days of enrollment), and how well the patient knows how to use the patient portal. Within 96 hours of a qualified emergency department visit, the research team will send a follow-up survey by text message to the patient that will assess patient’s perceived quality of emergency department pain treatment for this visit, how well they know how to use the patient portal, perceived ease of use of the E-IPP, patient and emergency department provider use of E-IPP during the last visit, satisfaction with the E-IPP, and intent to use the E-IPP for next emergency department vaso-occlusive episode visit. Patients will receive up to 3 follow-up surveys during the study period.

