### Data Analysis

#### Primary Outcome

The primary outcome is patient satisfaction with emergency department pain treatment through their perceived quality of emergency department pain treatment (Multimedia Appendix 2). This is measured with a composite of 3 questions developed based on the Adult Sickle Cell Quality of Life Measure Quality of Care measure [6]. The impact of the intervention on the primary outcome will be estimated using a linear mixed model. A 3-level model with random effects for site, participants nested within site, and site-to-site variation in the treatment effect and a fixed effect for treatment response will be specified to assess the impact of the intervention. The primary analysis will be based on the preintervention composite score and the score at 1 emergency department visit per participant, using the first visit for those with more than one. The model can accommodate multiple visits per participant by adding a covariance matrix to account for repeated observations.

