#### Other Outcomes

The secondary outcomes of hospital admission rate (a count outcome, as multiple hospital admissions are possible), 7-day emergency department vaso-occlusive episode revisit (a dichotomous outcome), and time to first dose, and other provider-level outcomes will be analyzed with generalized linear mixed models, where the outcome will be specified as a Poisson or binomial variable with a logit function as needed by the data type of outcome. The generalized linear mixed models would follow the same format as the linear mixed model with fixed effects for time, intervention, and covariates and random effects for participants within sites. The secondary outcome of satisfaction with IPP, measured with a single Likert scale question for both patient and provider, will be analyzed as a continuous outcome with a linear mixed model as detailed above for the primary outcome. In all cases, the analysis will estimate an intervention effect that will compare the secondary outcome at baseline to after the intervention is delivered. Power calculations indicate that the study sample will be too small to detect statistically significant differences in these noncontiguous variables, but estimates will be provided to inform future research.

The analysis of the quantitative readiness assessment result and the reach, adoption, implementation, and maintenance outcomes will be descriptive. As a preliminary attempt, at the end of the intervention, the results of the readiness assessment will inform our interpretation of the implementation and effectiveness outcomes. Sites with a lower level of readiness may face challenges during implementation, which will affect their implementation outcome and intervention effectiveness.

For qualitative interviews, the workgroup members will develop a codebook informed by the RE-AIM framework for data analysis. Using a deductive approach, the codebook will include an initial list of codes to be used in the analysis and definitions or operationalized examples for each code. Analysts will revise the codebook as necessary to hone definitions to increase consistency in coding across the research teams. Data will be compiled into different stakeholder groups by themes and analyzed across the study sites.

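### For the non-registry patients recruited during a hospitalization, the baseline visit will usually be one that ended in admission while the follow-up visit is not so selected; this tilts the admission comparison and may tilt the primary score

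*Protocol article*

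**What the plan says.** Under Patient Recruitment and Procedures, the first route is the registry: "All patients enrolled in the Sickle Cell Disease Implementation Consortium registry and screened as eligible will be contacted by research staff". Patients not yet in the registry are an additional source, and they "may be recruited in the clinic, during hospitalizations, or at community events by research staff". No share is given for any setting.

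The baseline measurement is tied to enrollment: "Each participating site will administer a brief patient baseline survey at the time of patient enrollment". It covers "patient-perceived quality of emergency department pain treatment for the last emergency department visit (within 90 days of enrollment"). Eligibility requires "At least 1 vaso-occlusive episode visit to the participating site’s emergency department within the past 90 days prior to enrollment", with no condition on how that visit ended.

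The follow-up visit is defined under Provider Recruitment as "the patient’s first emergency department vaso-occlusive episode visit of the month, after enrollment, within the 12 month study period for that patient", for a patient who has an embedded plan at that time. Disposition plays no part.

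On analysis, the Primary Outcome section states: "The primary analysis will be based on the preintervention composite score and the score at 1 emergency department visit per participant". For the secondary outcomes, which include hospital admission, "the analysis will estimate an intervention effect that will compare the secondary outcome at baseline to after the intervention is delivered". The Study Design section confirms that there is no control group. EHR Data Retrieval collects admission, revisit and readmission data from the 12 months of ED visits before enrollment and from the qualified visits after it.

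**The concern.** For a patient approached on the ward after coming in through the ED, the last ED visit is ordinarily the one that ended in the current admission. That patient's pre visit is in effect chosen by its disposition, and the post visit is not. Two things follow.

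- **Admission-type outcomes.** The pre-enrollment record of such a patient holds at least one admission because of how the patient was found. After enrollment nothing forces an admission, so the rate tends to fall without any intervention effect.
- **Primary score.** If a patient rates visits that end in admission lower than that patient's other visits, the baseline score is low by selection and the next score drifts back up. A comparison arm would share this drift. Here it would be counted as intervention effect, and a larger sample would not remove it.

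**Working it through.** The protocol article gives no figure for this effect. The benchmark is its 0.5 SD target difference.

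**Inputs from Statistical Analysis Power and Sample Size.** Within-site correlation is 0.10 and within-participant correlation 0.50. With total SD set to 1, site variance is 0.10 and the remaining 0.90 splits equally between patient and visit. Visit-level variance is 0.45, so SD_within = √0.45 = 0.671.

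**Assumed inputs (not in the document).**
- f: share of analyzed patients recruited in hospital whose rated visit led to that admission, 10% to 50%.
- p: admission chance per visit, 0.3 to 0.5.
- r: latent within-patient correlation between admission and a worse rating, 0 to 0.5.

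**Primary score.** Per affected patient, the expected change with no true effect is r × SD_within × φ(z)/p, where z is the normal quantile at 1 − p. The sample-average bias is f times that.

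At p = 0.4, z = 0.253, φ(z) = 0.386 and φ(z)/p = 0.966. With r = 0.3: 0.3 × 0.671 × 0.966 = 0.194 SD per affected patient. A simulation of this case with no true effect gave 0.192 SD.

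| f | Bias (SD) | Share of 0.5 SD |
|---|---|---|
| 10% | 0.10 × 0.194 = 0.019 | 4% |
| 25% | 0.25 × 0.194 = 0.049 | 10% |
| 50% | 0.50 × 0.194 = 0.097 | 19% |

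Over r = 0.1 to 0.5 and p = 0.3 to 0.5, the shift per affected patient runs from 0.05 to 0.39 SD. With f from 10% to 50%, the sample average is 0.005 to 0.19 SD. At r = 0 it is 0, and with the opposite sign of r it reverses.

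**Effect on the test.** Take the 0.447 SD of the random intervention effect on the total-SD scale (the article does not state the scale) and assume two-sided 5%. Then SE² = 0.447²/8 + 2 × 0.45/160 = 0.0250 + 0.0056 = 0.0306, so SE = 0.175. A bias of 0.05 SD raises false rejection from 5% to about 6%, and 0.10 SD to about 8-9%.

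**Admission.** No assumption about ratings is needed. With f = 25% and p = 0.30, the admitted share at the last pre-enrollment visit alone is 0.25 + 0.75 × 0.30 = 47.5%, against 30% afterwards, a gap of 17.5 points. But the retrieval spans 12 months. If each patient has 4 prior visits (assumed), one forced admission shifts the per-visit baseline rate by 0.25 × 0.70/4 = 0.044, about 4 points. At p = 0.40 it is 0.25 × 0.60/4 = 0.0375, again about 4 points.

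**The case against.** Several points on the other side carry weight.

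- **Enrollment may not happen on the ward.** The abstract says enrollment takes place in clinic or remotely, and the baseline survey is given at enrollment, so a patient may be approached in hospital and enrolled later. This softens the point but does not remove it: unless another ED visit has intervened, the admitting visit is still the last one.
- **The route is one of several.** Hospitalization is one of three settings named for non-registry patients. A reader might infer that the study's baseline as a whole is selected on a poor outcome. The text does not support that.
- **No link with ratings is shown.** The primary outcome is a three-question composite on perceived quality, and nothing in the article says that admitted patients rate ED pain treatment lower.
- **Large figures are easy to produce.** A reader might take f of 25-50%, p of 30-50% and a direct rating gap d of 0.3-0.8 SD, and get f × (1 − p) × d = 0.04 to 0.28 SD, up to 56% of the target. Those floors are assumptions, and only the within-patient part of the gap counts. At p = 0.3, a within-patient gap of 0.8 SD needs r = 0.8/(0.671 × 0.348/0.21) = 0.72, a very strong association.
- **The single-visit admission contrast overstates the problem.** Nothing makes one index visit the admission baseline, given the 12-month retrieval. The article also says the sample is too small for significance on these outcomes and offers them as estimates for later research.
- **The design's limits are acknowledged.** The Discussion concedes that an uncontrolled pre-post design has limitations. It does not mention this selection, which, unlike the missing control group, can be handled cheaply.

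**Conclusion.** The point holds for a subset, and the two kinds of outcome differ in certainty. For non-registry patients recruited during an admission that followed an ED visit, a recent admission in the pre-enrollment data is built in. The admission comparison is therefore biased toward improvement, by about 4 points on the assumed f = 25% and 4 prior visits. For the primary score the bias is conditional: roughly 0.02 to 0.10 SD (4% to 19% of the 0.5 SD target) at p = 0.4 and r = 0.3 for f between 10% and 50%, and zero or reversed if admission is unrelated to the rating or goes with better ones. Neither f, p nor r is in the article. That the rated visit is usually the admitting one is a reasonable inference from the recruitment and survey sections, not a statement in them.

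This does not show that the primary result will be materially inflated, and it is no reason to stop recruiting in hospital. It is worth acting on because the remedy is nearly free while enrollment continues and these patients cannot be separated later unless the setting is recorded.

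**What to change.** 1. In the tracking log that sites already keep (Participants and Eligibility Criteria), record the recruitment setting and whether the visit rated at baseline led to the admission during which the patient was approached.
2. For patients so identified, leave that visit and admission out of the baseline for the admission, revisit and readmission outcomes. The rest of the 12-month history stays in.
3. Pre-specify a sensitivity analysis of the primary outcome without these patients, and report their number beside it.

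The cost is a small addition to the log and a smaller sample, hence a wider interval, in the sensitivity analysis. The primary analysis set is unchanged. The hospital route should stay open: the disease is rare, sites must overenroll, and if hospital recruits are few the bias is negligible anyway.

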#### Provider Recruitment

All emergency department providers will be able to access the E-IPPs and will receive training on the protocol at staff meetings, resident conferences, or through emails. All emergency department providers will be invited to complete a baseline survey at enrollment with an information sheet introducing the study. If an enrolled patient participant has a qualified emergency department visit and the corresponding emergency department provider has not received training or completed the baseline survey, the study team will send a provider follow-up survey to the provider at enrollment with an information sheet introducing the study.

A qualified emergency department visit is defined as (1) a visit for an enrolled patient to a participating emergency department, the reason for the visit is a vaso-occlusive episode, and the patient has an E-IPP at the time of the emergency department visit; and (2) the patient’s first emergency department vaso-occlusive episode visit of the month, after enrollment, within the 12 month study period for that patient.

### Data Collection

The data collected in this study will consist of a readiness assessment; EHR data retrieval from patient records; patient baseline and follow-up surveys; provider baseline and follow-up surveys; and patient, provider, and emergency department administrator interviews. All measures (other than the readiness assessment) are matched with the RE-AIM framework (Multimedia Appendix 2).

### Readiness Assessment

The participating centers will administer a Readiness Diagnostic Scale (RDS) developed by members of the Consortium’s Implementation Research Committee at the beginning of the implementation period [35]. The RDS is a quantitative assessment to capture 3 interrelated dimensions of organizational readiness: general capacities (34 items), assessing participating emergency department’s existing emergency department practice and how it functions overall; intervention-specific capacities (13 items), assessing participating emergency department capacity to use the E-IPP; and motivation (17 items), assessing how well the emergency department facilitates physicians’ willingness to use the E-IPP.

Each site is required to have at least 5 total completed RDSs from a study team researcher, emergency department administrator, emergency department physician, and emergency department nurse to capture different system-level roles in clinical care.

### EHR Data Retrieval

Each participating site will perform EHR data retrieval for enrolled patients’ past 12 months ED visits and qualified ED visits to collect: hospital admission rate; 7- and 30-day emergency department revisit rate; 7- and 30-day hospital readmission rate; time to first dose of analgesic agent; and administered analgesic agent, dose, and route. At the end of the project, the site will also retrieve the following from the EHR: number of E-IPPs written and time of writing or updating, number of new E-IPPs available in the EHR and time of becoming available, and number of new patients at each site who are being offered access to their pain plan in the EHR after study enrollment targets are met. Data retrieval will follow a manual of procedures created by the workgroup to reduce bias [36,37].

### Patient Baseline and Follow-up Survey

Each participating site will administer a brief patient baseline survey at the time of patient enrollment that will assess patient demographic data, patient-perceived quality of emergency department pain treatment for the last emergency department visit (within 90 days of enrollment), and how well the patient knows how to use the patient portal. Within 96 hours of a qualified emergency department visit, the research team will send a follow-up survey by text message to the patient that will assess patient’s perceived quality of emergency department pain treatment for this visit, how well they know how to use the patient portal, perceived ease of use of the E-IPP, patient and emergency department provider use of E-IPP during the last visit, satisfaction with the E-IPP, and intent to use the E-IPP for next emergency department vaso-occlusive episode visit. Patients will receive up to 3 follow-up surveys during the study period.

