### Statistical Analysis Power and Sample Size

The study plans to have an analytical sample size of 160 patient participants, 20 for each site, for its primary outcome analysis. Each site is expected to enroll approximately 40 participants to reach the analytical sample size.

Sample size was calculated for the primary outcome, patient satisfaction with emergency department pain treatment through their perceived quality of emergency department pain treatment. For the power calculations, we used results from the Sickle Cell Disease Implementation Consortium needs assessment [17, 23], which used similar measurements to assess patient satisfaction with emergency department pain treatment. We assumed that the correlations between responses would not change and conducted a simulation to determine statistical power to detect a treatment difference of half a standard deviation. The sample estimation model has several assumptions: the intervention effect will vary across sites with the standard deviation for the random intervention effect set at 0.447; within-site correlation (commonly referred to as intercluster correlation) of baseline measurements, calculated as the ratio of site-level variance over the total variance, is set at 0.10; and within-participant correlation, calculated as the ratio of individual-level variance over total individual variance, is set at 0.50, reflecting the expectation that the preintervention composite score is predictive of the postintervention score.

Based on the Sickle Cell Disease Implementation Consortium registry data, we estimated that at least 50% of the study patient participants will have at least 1 qualified emergency department visit during the study period and that approximately 20% of the participants will be lost to follow-up and provide no posttest data. The total number of patients a site will recruit is approximately 40. The results indicate that the study will have >90% power to reject the null hypothesis when the intervention results in an average improvement in patient-perceived quality of emergency department care of 0.5 standard deviations under the assumed conditions.

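### The baseline primary score is tied to the last ED visit within 90 days without limiting it to a VOE visit at the participating ED, as eligibility and the follow-up score are limited

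*Protocol article*

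**What the plan says.** Four places in the protocol article bear on this.

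- **Baseline score** (Patient Baseline and Follow-up Survey). At enrollment the patient rates "patient-perceived quality of emergency department pain treatment for the last emergency department visit (within 90 days of enrollment". No reason for the visit and no hospital is named.
- **Eligibility** (Table 3, Patient participants). The patient must have had "At least 1 vaso-occlusive episode visit to the participating site’s emergency department within the past 90 days prior to enrollment".
- **Follow-up score** (same survey section). The patient rates "patient’s perceived quality of emergency department pain treatment for this visit", meaning the qualified visit. Under Provider Recruitment, a qualified visit is "a visit for an enrolled patient to a participating emergency department, the reason for the visit is a vaso-occlusive episode", with an individualized pain plan already in the record.
- **Primary analysis** (Data Analysis, Primary Outcome). "The primary analysis will be based on the preintervention composite score and the score at 1 emergency department visit per participant". The contrast is therefore between exactly these two ratings.

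The design has no control group (Study Design; Discussion).

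**The concern.** A pre-post comparison without controls relies on the two scores measuring the same thing under two conditions. Here the later score is fixed to one kind of visit at one kind of place, and the earlier one is not. The eligibility rule guarantees that a suitable visit exists in the window, but not that it is the latest ED visit.

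Take a patient treated for a VOE at the study ED 60 days before enrollment and at an outside hospital 10 days before. That patient is eligible and, on the words given, rates the outside hospital at baseline and the study ED at follow-up. Any difference between the two hospitals is then counted as change due to the intervention, and nothing in the design separates the two.

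**Working it through.** **Step 1: the definitions side by side**

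| Use | Reason for visit | Hospital | Which visit |
|---|---|---|---|
| Eligibility | VOE | participating site's ED | at least one in the past 90 days |
| Baseline score | not stated | not stated | the last within 90 days |
| Follow-up score | VOE | a participating ED | the qualified visit; the first is used in the primary analysis |

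The eligibility and baseline rows select the same visit when the patient's latest ED visit was a VOE visit to the study ED. They differ when a later ED visit in the window took place elsewhere or for another reason.

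**Step 2: which mismatch is plausible**

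A VOE treated at an outside hospital fits the baseline wording fully. The article expects outside use, because its Intervention section describes patients showing their plan to ED staff elsewhere in the country. A visit for a complaint other than pain is a poor fit, because the item asks about pain treatment. The different-hospital route is therefore the main one.

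**Step 3: size of the possible shift**

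The article states no figure for this, so there is none to reproduce. Let *f* be the share of analysed participants whose baseline rating concerns another visit. Let *g* be the mean rating of those visits minus the mean rating that the same patients would give their study-ED VOE visit, in SD units.

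- Baseline mean = intended baseline mean + *f* × *g*
- Estimated change = intended change − *f* × *g*

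A negative *g* (other visit rated worse) inflates the estimate, and a positive *g* shrinks it. Both inputs are assumptions. The comparator is the design target, an "average improvement in patient-perceived quality of emergency department care of 0.5 standard deviations".

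| *f* (participants of 160) | size of *g* | shift, either sign | share of 0.5 SD |
|---|---|---|---|
| 0.10 (16) | 0.5 | 0.10 × 0.5 = 0.05 SD | 10% |
| 0.20 (32) | 0.5 | 0.20 × 0.5 = 0.10 SD | 20% |
| 0.30 (48) | 0.5 | 0.30 × 0.5 = 0.15 SD | 30% |

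A wider set of assumptions runs from 0.10 × 0.25 = 0.025 SD to 0.30 × 1 = 0.30 SD. If *f* or *g* is zero, there is no shift.

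**Step 4: effect on precision**

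Mixed reference visits could also weaken the pre-post correlation, planned at 0.50. As an approximation, SE² = τ²/8 + 2σ²(1 − r)/160. Here τ = 0.447 is the between-site SD of the effect, σ² is 0.9 of the total variance (within-site correlation 0.10), and two-sided alpha of 0.05 is assumed. The article does not give the scale of τ, so two scalings are shown, with normal-approximation power for 0.5 SD.

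- Total variance 1, r = 0.50: SE² = 0.0250 + 0.0056, SE = 0.175, power 81.5%. With r = 0.30, power is 78.8%.
- Total variance 2, r = 0.50: SE = 0.190, power 96.0%. With r = 0.30, power is 93.9%.

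The stated power of more than 90% is reached on the second scaling and not on the first. This point does not depend on which is right. On either scaling the loss is 2 to 3 percentage points, so the matter is one of possible bias, not of power.

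**The case against.** The best reply is that this is shorthand. The 90-day parenthesis repeats the eligibility window, so the natural reading is that the eligibility visit is meant. The article also drops qualifiers elsewhere without ambiguity: the Primary Outcome section speaks of one ED visit per participant, and nobody would take that as any visit anywhere. In addition, the questionnaire, the manual of procedures and the outcomes appendix are not shown, and any of them may fix the visit exactly.

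Much of this stands. The article nowhere says that visits of any kind or at other hospitals are to be rated, and a reader should not infer such a rule. What is left is narrower. The follow-up visit has a defined term behind it, so shorthand there is harmless; the baseline visit has none. The article does not leave the baseline visit to another document either. It states one, more loosely than its own neighbouring definitions.

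A reader might also infer that the mismatch flatters the intervention, on the view that an outside ED without the patient's plan would be rated lower. The documents do not support a direction. Table 1 and Study Setting show that before the study only 2 of the 8 EDs had plans embedded in the record. The others had none, or had them only in clinical notes or on a secure server. The baseline gap between study and outside EDs could go either way.

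Finally, the study is already enrolling, so a changed prompt would leave two versions of the baseline score. That is a real cost and belongs with the fix.

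**Conclusion.** The point holds as a looseness in the definition of the primary outcome. The baseline visit is not limited to a VOE visit at the participating ED, while eligibility and the follow-up score are. Followed literally, some patients could rate different hospitals before and after, and the uncontrolled design would count the difference as effect.

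The text does not show that this is happening, how often, or in which direction. The figure of 0.05 to 0.15 SD up or down rests wholly on an assumed 10% to 30% share and an assumed gap of 0.5 SD. It shows that the possible shift is not negligible beside the 0.5 SD target; it is not an estimate of bias. If the survey or manual already names the right visit, only the sentence in the article needs correcting. The point is worth settling because it touches the primary comparison and every enrolled patient already has a suitable visit to refer to.

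**What to change.** 1. Define the baseline reference visit as the patient's most recent VOE visit to the participating ED within the 90 days before enrollment. The eligibility rule ensures that every participant has one, so nobody is lost.
2. Check the survey and manual of procedures. If the item does not already name that visit, reword it to do so, preferably with the visit date.
3. Record which wording each participant received.
4. For participants already enrolled, use patient report together with the EHR to identify those whose rated visit was a different one, and add a sensitivity analysis of the primary model without them. Patient report is needed because a site's own records may miss outside visits. The planned EHR retrieval of the past 12 months of ED visits should help to date the study-ED visits.

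**Cost.** One line of survey wording, one extra variable and one extra model run. Some patients will rate a slightly older visit, still within 90 days. If the wording changes during enrollment there will be two prompt versions; item 3 allows results to be compared between them.
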